Each hospital and HHC agency dyad will assemble a site implementation team comprised of key stakeholders and project champions involved in the planning and implementation. The principal investigator and at least two other research team members will visit each site in person and stay in close phone or email contact with the site coordinator and team for onboarding and Aim 2 data collection. Additional contacts may occur if needed. We have planned 12 in-person visits and frequent, standardized phone, virtual and/or email contacts. Expected site stakeholders may include, for example, a programmer to write a query to identify the inpatient sepsis survivors; hospitalists, emergency room physicians, sepsis experts, and ambulatory providers to determine follow-up appointment workflow, and hospital case managers are expected to be important informants overall. On the HHC side, the teams will include a hospital based HHC liaison who facilitates the referrals and transfer of patient information to the HHC agency; an HHC intake nurse who schedules the first visit and assigns the visiting nurses; a HHC nurse who knows the workflow for planning visits and working with patients; an intake director who understands the entire workflow; the Directors of Nursing or Chief Operating Officers who oversee operations. These stakeholders will participate in individual, or group interviews and survey completion as described below. An estimated 60 stakeholders will provide informed consent prior to data collection. A study site coordinator identified by each dyad will assist with communication, scheduling, oversight, and data collection at each site. A project manager will track progress and support the work across all sites. Stakeholder consent to participate will be obtained prior to each interview by the study team member conducting the interview.

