### Study sample

#### Aim 1, effectiveness of the I-TRANSFER intervention

Sample sizes needed to provide sufficient power were calculated using Stata [79]. Preliminary unpublished data of a national sample show on average a 23% 30-day readmission rate for sepsis survivors in HHC. Our previous study showed a 7-percentage point or 41% relative reduction among those receiving early visits [24], and other studies report that 22–45% of readmissions are preventable [80]. Therefore, to detect a 7-point reduction (30.4% relative decrease) in the readmission rate under the intervention we would require an average of 400 patients per time interval. Current estimates from the sites give us 869 per period.

The I-TRANSFER intervention is targeted at the hospital and HHC agency and is considered part of clinical care implemented for all sepsis survivors. There is no individual patient recruitment, prospective assignment, or primary data collection from patients. The analysis will be completed on existing datasets. We will analyze a sample drawn from all Medicare fee-for-service sepsis survivors discharged to HHC during a 4-year period (01/01/2021 and 12/31/2024). Analyses from our 2013–14 dataset suggests that without exclusions there will be approximately 800,000 sepsis discharges per year who receive HHC [24].

Ten clinical sites located in the United States have committed to participate as dyads, 5 referring hospitals and their 5 partnered home health agencies. Sites were selected based on our relationships with staff, ownership status (hospital owned or free-standing), commitment to appoint an implementation team, size, geography, and diversity (academic and community). We sought regional diversity with sites in the East and West. To be eligible HHC agencies must be Medicare certified to generate claims and confirm a hospital referral source as a partner.

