### Data sources and collection

#### Aim 1, effectiveness of the I-TRANSFER intervention

A national sample of Medicare administrative, home health OASIS and claims data from CMS Chronic Condition Warehouse (CCW) will be employed (Table 1). This will yield detailed information about the index hospital stay, subsequent HHC and outpatient provider services and outcomes. It also will provide information about the characteristics of hospitals and admitting HHC agencies, and the health care market areas where patients live. The CCW maintains calendar year files so we will request files between 01/01/2021 and 12/31/2024. We will request CCW data on all Medicare beneficiaries with a claim for a HHC service provided one year prior to the start of the study to 6 months after the end. Within these data sets, we will identify the sepsis survivors transitioned from participating hospitals to their partner HHC agency by merging the Provider of Service File with the claim files. The additional sepsis survivors found in the CCW data, not associated with our participating institutions, will serve as additional controls.

**Table 1 Tab1:** Variables Obtained from the Medicare Claims and OASIS Home Health Admission Files

Data	Source
*Physician, Home Health Agency and Hospital Characteristics*	
Physician specialty	Downloadable National Provider Identifier File (CMS)
Home Health Agency and Hospital Ownership	Provider of Services File
Home Health Agency and Hospital Control/auspices (for- profit/non-profit/public)	Provider of Services File
Size of home health agency, # of annual admissions	Provider of Services File
*Beneficiary Sociodemographic, Clinical and Cost Variables*	
Demographics	Medicare Beneficiary Summary File; OASIS
Informal support	OASIS
Living arrangements	OASIS
Eligible for Medicare and Medicaid	Medicare Beneficiary Summary File
Health care use and cost (ie. Medicare program payments)	MedPAR/Medicare Parts A and B SAF claims
Medical diagnoses ICD codes, acute and HHC	MedPAR/Medicare Parts A and B SAF claims; OASIS
Index hospital length of stay	MedPAR
Cognitive, physical, sensory function	OASIS
*Early Nursing and Outpatient Provider Visits Following Index Hospital Discharge*	
Timing and number of home health visits	Medicare Home Health SAF claims
Timing of first physician, physician assistant or nurse practitioner visit for outpatient evaluation & mgt	Mediare Part B SAF claims

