### Analysis

#### Aim 1, effectiveness of the I-TRANSFER intervention

A key initial task is the identification of all sepsis survivors in the national hospital dataset. Consistent with our prior work, we will use two complementary strategies to identify sepsis survivors. First, we will use the explicit International Classification of Diseases 10th Revision (ICD-10) codes (A40-41, R65.2). Second, we will employ the implicit approach used in our previous study and developed by Angus and colleagues [88] that requires a code for infection and end-organ dysfunction. Among them we will identify the sepsis survivors transitioned from participating hospitals to their partner HHC agency during the study timeframe by merging the Provider of Service File with the claim files.

Each hospital discharge of a sepsis survivor to HHC will represent a separate record on the timeline file. Some Medicare beneficiaries will have more than one index hospital discharge during the study period. Data available will give us the flexibility to define an “index” hospitalization in several ways. Our main approach will be to analyze all eligible hospitalizations followed by HHC and to adjust for the potential effect of clustering at the patient and provider level. We plan to examine the sensitivity of our results to alternative specifications of the “index” hospital stay including analyses based on a single index hospitalization per person.

Deidentified Medicare claims will be the source of information used to construct Aim 1 outcomes of rehospitalization, total hospital days if readmitted and ED utilization. The CMS claims will be stored a secure, password protected site. The CMS approach to identifying hospital readmissions was successfully used in our heart failure and sepsis studies and we will use the same approach to identify readmissions in this study [24, 50]. Observations on sepsis survivors in the baseline period will be used to check balance on covariates identified by the Andersen Behavioral Model. Any remaining imbalance will be considered by including covariates in the hierarchical regression analysis.

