In addition to the survivors from the treated dyads in the baseline period, additional control survivors will be used to provide a much larger sample of control observations. These observations will be drawn from the population of Medicare sepsis survivors not being cared for by any of the participating institutions. This sample is unlikely to be balanced on covariates, a priori, with the sample of survivors from participating providers. Therefore, entropy balancing will be used to create sampling weights for these observations to produce balance on covariates. All hierarchical regression analyses will take these entropy balance weights into account. In addition to an intent-to-treat indicator, the regression will include covariates specified by the Andersen Behavioral Model. Inpatient days after the index discharge will be modeled using hierarchical Poisson regression. ED utilization will be modeled using hierarchical logistic regression.

The pragmatic aspects of the study design make it important to conduct various sensitivity and exploratory analyses. Sensitivity analyses will include checks of robustness of findings with and without sepsis survivors who are readmitted shortly after discharge (e.g., within 7 days), those with a resumption of HHC episode, discharges with very short (1 day) or very long hospital stays (30 days or more), and survivors less than 65 years old. Exploratory analyses will include estimation stratified by type of sepsis, sex (as a biological variable), and hospital ownership status.

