## Discussion

Sepsis takes more lives than opioid overdoses, breast cancer, and prostate cancer combined [4]. Prior studies by our team indicate the impact of early HHC nursing combined with early outpatient provider visits but the ability of hospitals and HHC agencies to implement these effective interventions is limited and varied. Our innovative study will be the first to transform the practice paradigm in HHC through implementation of a best practice early visit intervention for growing numbers of sepsis survivors. This study will bring process and structure to a very common transition process – currently many HHC agencies do not have the resources to study how to optimize transition of care processes, our findings will inform the industry and can apply to other disease states. The study focuses on an understudied process (transition to and care in HHC) and an understudied population (sepsis survivors) to tackle a large, costly, and common readmission challenge where little evidence exists.

Our study, however, is not without limitations. It is possible that dyads may begin to implement parts of the protocol prior to the implementation period. However, we believe the specifications of the I-TRANSFER components will be difficult to achieve in full and effectively without collaborative efforts. To be safe, additional specification checks will include treatment indicators in the retrospective control data and onboarding period to determine whether such activities were taking place. We will also ask the status and quality of such interventions prior to onboarding and would recruit a new dyad if it is an issue.

Also, the sample of sepsis survivors from non-participating dyads is a useful comparison group only if the distributions of characteristics of those survivors and their care providers overlap/match with those of survivors from the participating dyads. By using the entire Medicare population, the risk of lack of overlap is minimized. Nevertheless, should lack of overlap be an issue, we will use matching techniques to mitigate this threat. Lastly, we considered a cost analysis but due to budgetary constraints could not include a robust analysis. Instead, we will document whether there are added costs to the dyads such as adding a position, and we will have the data from the claims to roughly compare differences in service utilization such as numbers of HHC visits, outpatient care, or observation stays.

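### Dyad patients must follow the partner hospital-to-agency route but national controls may follow any route, so a partnership difference can enter the I-TRANSFER estimate

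*Protocol article*

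**What the plan says.** **Dyad patients.** In the protocol article (Data sources and collection, Aim 1), "we will identify the sepsis survivors transitioned from participating hospitals to their partner HHC agency". The Analysis section for Aim 1 repeats the rule: "Among them we will identify the sepsis survivors transitioned from participating hospitals to their partner HHC agency during the study timeframe". The Study sample section makes the link a condition of site eligibility, since an agency must "confirm a hospital referral source as a partner".

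**National controls.** Data sources and collection says "The additional sepsis survivors found in the CCW data, not associated with our participating institutions, will serve as additional controls". The Analysis section says "These observations will be drawn from the population of Medicare sepsis survivors not being cared for by any of the participating institutions". Neither sets a hospital-agency condition. The Discussion nevertheless calls this group survivors from non-participating dyads: "the sample of sepsis survivors from non-participating dyads is a useful comparison group only if" the characteristics of survivors and their providers overlap or match. No control dyad is defined anywhere.

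**Baseline dyad patients.** Study design makes survivors who went to the participating agencies before implementation the usual-care control group. It does not name the hospital they came from.

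**Model and balancing.** The Analysis section describes hierarchical regression with one intent-to-treat indicator, Andersen-model covariates and entropy weights for the national patients. Clustering is handled at patient and provider level, and the Study period section adds adjustment for time. Table 1 lists ownership, control and agency size as agency and hospital variables. The Conceptual framework adds hospital ownership of the agency and chain status.

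**The concern.** The two groups meet different entry rules. A dyad patient satisfies a joint condition on hospital and agency. A national control needs only a sepsis discharge followed by home health care elsewhere, so that pool mixes linked and unlinked transitions.

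The plan itself treats the handoff as the thing to be changed, and among the expected site stakeholders it lists "a hospital based HHC liaison who facilitates the referrals and transfer of patient information to the HHC agency". If usual care on partner routes differs from usual care on other routes, entropy balancing will not remove the difference, because the link is not among the variables supplied. Ownership is only a partial proxy, since the sites were chosen to include free-standing agencies.

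Two things are at stake. A constant difference between routes could be partly credited to, or subtracted from, the intervention. A difference in time trend between routes could be mistaken for an effect, because with staggered rollout abandoned there are no unexposed dyad patients in the intervention year.

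**Working it through.** **Inputs from the documents.** Usual-care readmission is 23%, the target reduction is 7 points, and the sites expect 869 patients per period in five dyads (all Study sample). The plan's relative figure reproduces: 7/23 = 30.4%. The plan gives no figure for a partnership difference, for the ICC, or for the share of discharges that go to partner agencies. Those values are assumed below.

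**Step 1: which contrast carries the offset.** Let partner routes differ from the national pool by a constant d under usual care.
- Within dyads, intervention minus baseline: d is on both sides and cancels.
- Dyads minus national in the intervention year: d enters in full.
- The planned model mixes the two contrasts, so the question is how much weight the second receives.

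**Step 2: share of d entering the estimate under the named model.** I use a linear random-intercept approximation with one intercept per provider unit, equal baseline and intervention numbers, a true effect of zero and no dyad/national term. The national pool is large enough to fix the intercept and time effect. With n patients per dyad per period and intraclass correlation ρ, the generalized least squares coefficient on the intent-to-treat indicator contains

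share = (1 − ρ) / (1 − ρ + nρ), with n = 869/5 ≈ 174.

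| Assumed ρ | Calculation | Share of d |
|---|---|---|
| 0 | 1/1 | 1.00 |
| 0.005 | 0.995/(0.995 + 0.87) | 0.53 |
| 0.01 | 0.99/(0.99 + 1.74) | 0.36 |
| 0.02 | 0.98/(0.98 + 3.48) | 0.22 |
| 0.05 | 0.95/(0.95 + 8.70) | 0.10 |

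Solving the full system numerically with 100 to 5,000 national providers gave the same shares. Adding a dyad/national term gave 0.00 at every ρ.

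**Step 3: an illustrative size for d.** Suppose timely-visit receipt under usual care is 10, 20 or 30 percentage points higher on partner routes, and that timely visits lower readmission by the plan's 7 points. Then d = 7 × 0.10, 0.20 or 0.30 = 0.7, 1.4 or 2.1 points. Multiplying by the shares for ρ from 0.05 to 0.005:
- smallest: 0.10 × 0.7 = 0.07 points;
- largest: 0.53 × 2.1 = 1.11 points, or 1.11/7 = 16% of the target.

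The opposite sign is equally possible.

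**Step 4: ceiling for a constant offset of that size.** Compare 869 exposed patients only with a very large national pool, without clustering. The standard error is √(0.23 × 0.77/869) = 1.43 points. A two-sided 5% test with no true effect would reject in 7.8%, 16.5% and 31.3% of trials for d = 0.7, 1.4 and 2.1. These rates use neither the baseline dyad patients nor the planned clustering adjustment, so they bound the problem and do not describe the planned analysis.

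**Step 5: trends.** If usual-care readmission changes by an extra δ points on partner routes between baseline and intervention, a difference-in-differences contrast equals the true effect plus δ. The dyad/national term does nothing about δ. Only national controls that resemble the dyads in route can reduce it.

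**The case against.** The strongest reply is that the same-route control already exists. Baseline dyad patients are the usual-care group, and national patients are added to them to address historical threats and improve generalizability. That stands, and it removes a constant difference from the within-dyad contrast.

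A reader might infer that any partnership advantage is necessarily built into the I-TRANSFER estimate, or that false-positive rates of 8% to 31% are to be expected. The documents do not support either. Nothing says that partner routes deliver more timely care. The liaison appears only in a list of expected stakeholders, and nothing says other hospitals lack one. The rejection rates treat the national pool as the sole comparator. Nor do the documents show, or exclude, that the intervention changes who is sent along the partner route.

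Other safeguards deserve credit: provider-level clustering, time adjustment, three comparison windows, and matching if overlap fails. The Discussion also plans treatment indicators for the retrospective and onboarding periods. The gap between the intervention and retrospective coefficients would in fact be a difference-in-differences. However, these indicators are offered as specification checks for early adoption, not as the estimate.

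Finally, an analysis plan may add a dyad term and finer control rules. That limits how hard the missing term can be pressed. It does not change the entry rules, which the article states twice for each group and which do not fit its own description of the controls as non-participating dyads.

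**Conclusion.** The asymmetry in entry rules is real, and no listed covariate measures the hospital-agency link. Its consequence is conditional. A stable partnership difference can enter the estimate through the pooled model with one intent-to-treat indicator. The share is about 10% to 53% for assumed ICCs of 0.05 to 0.005, nearly all of it at ICC 0, and none once a dyad/national term is present. With assumed offsets of 0.7 to 2.1 points this is roughly 0.1 to 1.1 points against a 7-point target. A trend difference between routes is not bounded by these figures and survives the added term.

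The shares rest on a linear approximation to a generalized mixed model, equal period sizes and no modelling of the entropy weights. The offsets, their sign and the ICC are assumptions. The point justifies a change to the control definition and the model. It does not show that the study will be biased in favour of the intervention.

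**What to change.** 1. From baseline-year claims, derive for each hospital-agency pair the share of the hospital's sepsis discharges to home health care that the agency receives. Either restrict national controls to pairs whose share lies in the range seen in the five dyads, or include the share in the entropy balancing. This avoids assuming that a partner is its hospital's largest receiver.
2. Use the hospital-agency pair as the provider unit in both groups. Add a dyad, or dyad/national, term so that the intent-to-treat coefficient is a difference-in-differences contrast.
3. Compute the weights within calendar quarter.
4. Keep the any-route national pool as a sensitivity analysis.
5. Reconcile Study design, which defines baseline controls by participating agency without naming the hospital, with the partner-route rule in Data sources and Analysis.

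The cost is one derived variable from claims already requested and some plan wording. The control pool becomes smaller, but the plan projects about 800,000 national discharges a year before exclusions. Even if only 1% remained, that would be 8,000 a year against 869 dyad patients per period. Some generalizability is lost in the main analysis; the any-route sensitivity analysis retains it.

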#### Aim 2, I-TRANSFER implementation

Data for Aim 2 will be generated through three sources: by administering the Organizational Readiness for Implementing Change (ORIC) survey, a needs assessment at each site, and the Consolidated Framework for Implementation Research (CFIR) interviews.

### Organizational Readiness for Implementing Change (ORIC) survey

At baseline, each acute care and home health stakeholder will complete the ORIC 12-item survey to assess readiness for change that refers to organizational members' shared beliefs in their collective capability to change (change efficacy, items 1,3,5,7,9,11) and their shared resolve to implement a change (change commitment, items 2,4,6,8,10,12). Based on a 5-point Likert scale of agree to disagree, the tool has high inter-item consistency, inter-rater reliability, inter-rater agreement, good model fit and item loadings. The ORIC score is calculated by summing across all items. Lower scores represent less organizational readiness for implementing change; higher scores represent a more favorable readiness for implementing change [59].

Implementation Mapping. The systematic process of implementation mapping has 5 steps for developing strategies to improve adoption, implementation, and maintenance of evidence-based interventions in the real world [64]. These steps will be informed by the needs assessments, the CFIR interviews with stakeholders and the ORIC survey. Step 1 calls for an implementation needs assessment of eight objectives to identify barriers and enablers, adopters, and implementers (Table 2). At the end of this step, we will know who the champions will be, who will make resources available, and who are the decision makers. In Step 2, together with the dyads, we generate adoption and implementation outcomes and performance objectives, identify determinants, and create matrices of change objectives. This step determines who must do what and how will success be measured. For example, the hospital case managers may be tasked with determining the workflow and strategies for making the follow-up outpatient appointment and educating sepsis survivors on its importance. Matrices of change objectives answer what must change to make something happen [64]. Each performance objective related to I-TRANSFER (e.g., identify the survivors, communicate with HHC, make the appointment, etc.) and its determinants, identified in earlier steps, will be placed on a grid with corresponding person(s) responsible. Third, we will select implementation strategies for each component of I-TRANSFER. In addition to using our teams’ wisdom, we will turn to the literature using resources such as the taxonomy of theory-based methods applicable to individual and organizational levels [70, 79, 81–83]. While the exact strategies to be employed will depend on the findings of this period of data collection, it is likely that they will consist of a multifaceted approach to implementation including staff education via webinar or in-person, changes to organizational processes and workflow, information technology, and the provision of audit and feedback to clinicians and staff taking part in the implementation study. Fourth we will produce implementation protocols, and in the fifth step we will monitor progress and fidelity during the 12-month implementation phase. While maintaining the core I-TRANSFER elements, in keeping with a pragmatic design, we will allow variation in the workflow for dyad preferences while providing monitoring and feedback of the implementation through the rollout [84]. Implementation mapping is an iterative process where steps will be revisited and modified as needed [64].

**Table 2 Tab2:** Needs Assessment Objectives and Questions

Objective 1. Understand current acute care processes for identifying sepsis patients
